#### Colon cancer screening

Logistic-type regression will be used to test the hypothesis that those assigned to patient navigation intervention will have significantly higher CRC screening rates compared to those randomized to the lifestyle intervention at six months. Clustered sampling effects due to site and physician will be incorporated using a multilevel modeling approach.

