#### Advantages of the study design

This innovative research design will allow each intervention to serve as the control for the other. Specifically, the MINT arm will be the control condition for the PN arm, and vice-versa, in that the MINT intervention arm will receive usual counseling for colon cancer screening, and the PN arm will receive usual counseling about appropriate lifestyle changes to improve BP. We believe this novel, simultaneous testing of two community-based interventions in a randomized fashion is an economical and yet rigorous strategy that enhances the acceptability of the project to the community because all participating men will receive a potentially beneficial intervention (that is, no one receives a ‘placebo’. See Figure 
1). The MINT intervention will be conducted by trained research assistants, while the PN intervention will be delivered by trained community health workers. Assessments are conducted at the baseline (visit 1) and six months follow-up (visit 2).

Though we are testing interventions simultaneously within the same trial, we do not see the interventions as tackling BP and CRC in tandem. The intervention for BP is distinct from the intervention for CRC, even though the interventions are being tested simultaneously. If these interventions prove successful in our study, successful translation of these interventions would not necessitate that the BP and CRC interventions be delivered together, as they are not delivered together in the study. The interventions are not necessarily complementary, but were chosen because they are similarly high-impact public health problems for black men, and are conducive to community-based delivery in a population that is under-represented in primary care clinical settings.

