#### Challenges of the study design

Given that randomization will occur at the level of the individual, and the socially interactive nature of the recruitment setting, wherein participants randomized to different arms will presumably talk to each other, there is potential for some between-arm contamination, which may dampen the observable results in either arm. To address this potential threat to the validity of the study design, we have added important safeguards to minimize contamination. First, both the MINT and PN interventions are highly tailored to address participant’s specific concerns and barriers through individualized counseling strategies implemented over multiple sessions. Each intervention includes several interdependent components, reflecting a complexity that significantly reduces each arm’s vulnerability to contamination. These intervention characteristics, along with the complexity of the target behaviors (lifestyle changes for BP control or colonoscopy) make it unlikely that any exposure to activities, participants or interventionists across study arms would have a significant effect on individual outcomes. Second, we have employed an additional safeguard to minimize contamination: MINT interventionists will be trained separately from PN interventionists, and each interventionist will be trained to do MINT only or PN only. There will be no “cross-training”, thereby minimizing “bleed” of one intervention into another.

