#### Randomization

Following the determination of eligibility, consent procedures, and completion of baseline self-report and psychosocial measures, individual-level randomization will occur via a randomization table generated by the study statistician. Participants will be randomized in 1:1 ratio to either the MINT lifestyle intervention or the CRC patient navigation intervention.

Participants will be informed of the results of randomization by an RA at the time of the baseline interview. At this time, the RA will discuss the MINT or the PN intervention/counseling session schedule, and answer any additional questions. Given the nature of the intervention, it is impossible to blind the RAs to the assigned condition. However, the dimension that the RA’s knowledge of the assigned condition could possibly affect is the BP measurement - one of the primary outcomes of this study. To reduce the potential for this bias, we will use an automated BP device (Vital Signs Monitor 300 Series; Welch Allyn; Skaneateles Falls, NY, USA). The other primary outcome, receipt of colon cancer screening, cannot be influenced by the RA’s knowledge of the assigned condition.

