### Analysis

#### Sample size and power calculations

The sample size is based on the number of participants needed to provide adequate power to test the primary hypothesis, that is, to detect the hypothesized group differences in the primary outcomes. Based on our own clinical experience and estimates from other clinical trials in uncontrolled hypertensive patients
[4-6,11,63] we estimate that the cross-sectional standard deviations (SD) of SBP and DBP at baseline will be about 15/12 mm Hg. Conservatively, assuming (a) that the SD at follow-up will be 25% larger in the MINT group, (b) that the correlation between baseline and follow-up BPs will be 0.6 in the CRC patient navigation group and 0.4 in the MINT group (both due to heterogeneity of treatment response), and (c) that there are no barbershop effects (as this is an individual level intervention) on the change in BP, 200 participants per group will provide 86% power to detect a 5 mmHg differential change in SBP and the same power to detect a 4 mmHg differential change in DBP, based on testing the Time X Group interaction in a MANOVA, allowing for heterogeneous variances and serial correlations
[64]. Regarding the CRC navigation arm, a sample size of 127 participants per group is needed to provide 90% power to detect a group difference in the rate of completed CRC screening at six months from a baseline rate of 35%
[26,27,32,65] to a desired level of 60%. Consequently, we will recruit 240 participants per intervention group (allowing for 20% attrition), which will provide sufficient power to detect the hypothesized difference in both arms of the study. Power analyses were conducted using the R statistical language
[64,66].

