### Analysis of the primary aims

#### Blood pressure

MANOVA will be used to test the hypothesis that those assigned to MINT counseling will, on average, exhibit greater six-month decreases in SBP and DBP than those assigned to the CRC patient navigation condition. This analysis will have one within-person factor - Time (baseline vs. six-month follow-up) - and one primary between-persons factor (Treatment Group). The outcome measure in this analysis will comprise a linear combination of systolic and diastolic BP.

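### Interventionists are nested in arm but absent from both primary analyses; if outcomes vary by interventionist, intervals will be too narrow and type I error above 5%

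*Protocol article*

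**What the plan says.** **Delivery.** Under Advantages of the study design: "The MINT intervention will be conducted by trained research assistants, while the PN intervention will be delivered by trained community health workers". Under Challenges of the study design, as a safeguard against contamination: "each interventionist will be trained to do MINT only or PN only". The intervention sections describe individual counselling: four MINT sessions, or at least two navigation sessions with weekly contact where a man has several barriers.

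**Allocation.** Under Randomization: "individual-level randomization will occur via a randomization table generated by the study statistician", in a 1:1 ratio.

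**BP analysis.** Under Analysis of the primary aims, Blood pressure: "This analysis will have one within-person factor - Time (baseline vs. six-month follow-up) - and one primary between-persons factor (Treatment Group"). No cluster level is named.

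**CRC analysis.** Under Colon cancer screening: "Clustered sampling effects due to site and physician will be incorporated using a multilevel modeling approach". The interventionist is not among the levels.

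**Power.** Under Sample size and power calculations, one assumption is "that there are no barbershop effects (as this is an individual level intervention) on the change in BP". On that basis 200 men per group give 86% power for a 5 mmHg difference in systolic change. Interventionist effects are not mentioned.

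**The concern.** Men counselled by the same person share whatever that person does well or badly. Each interventionist serves one arm only, so any such variation goes straight into the difference between arms.

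The levels that the CRC model does name do not stand in for it. Men are randomised individually, so barbershops cross the arms, and no physician delivers either intervention. The reason given for ignoring barbershop effects, that treatment is delivered to individuals, does not cover counsellor effects, which arise from individual delivery.

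At stake is whether an arm difference produced by a few strong or weak counsellors could be reported as an effect of the intervention, with an interval that leaves out that source of uncertainty. This matters because the article aims at community translation, which is a claim about the interventions and not only about the staff who happened to deliver them.

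**Working it through.** **Inputs from Sample size and power calculations.** Baseline systolic SD 15 mmHg; follow-up SD 25% larger in the MINT group (18.75); correlations 0.6 (navigation) and 0.4 (MINT); 200 per group; target difference 5 mmHg; CRC comparison rate 35%.

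**Assumptions.** The article states no alpha, number of interventionists or ICC. I take two-sided 5%, k = 4 to 8 interventionists with equal caseloads in the arm that targets the outcome, clustering in that arm only, and ICC 0.01, 0.02 and 0.05.

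**Step 1: reproduce the plan's figure.** Variance of change = SD0² + SD1² − 2·r·SD0·SD1.
- Navigation: 225 + 225 − 2(0.6)(15)(15) = 180.
- MINT: 225 + 351.56 − 2(0.4)(15)(18.75) = 351.56.
- SE = √((180 + 351.56)/200) = 1.630.
- Power = Φ(5/1.630 − 1.96) = 86.6%.

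This matches the stated 86% and treats all men as independent, so it contains no allowance for interventionists. For diastolic pressure the variances are 115.2 and 225.0. Their ratio is the same (225.0/115.2 = 351.56/180 = 1.953), so the results below apply to it equally.

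**Step 2: type I error of the unadjusted test.** With m = 200/k men per interventionist, DEFF = 1 + (m − 1)·ICC. The variance of the arm difference is inflated by
- BP (MINT clustered): F = (180 + 351.56·DEFF)/531.56
- CRC (navigation clustered, equal rates under the null): F = (1 + DEFF)/2

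and the actual type I error is 2·(1 − Φ(1.96/√F)).

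Example for BP, k = 4, ICC 0.01: m = 50, DEFF = 1.49, F = (180 + 523.8)/531.56 = 1.324, and 1.96/√1.324 = 1.703, giving 8.9%. With k = 8: DEFF = 1.24, F = 1.159, giving 6.9%.

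| ICC | BP, k = 8 | BP, k = 4 | CRC, k = 8 | CRC, k = 4 |
|---|---|---|---|---|
| 0 | 5% | 5% | 5% | 5% |
| 0.01 | 6.9% | 8.9% | 6.4% | 7.9% |
| 0.02 | 8.8% | 12.7% | 7.8% | 10.8% |
| 0.05 | 14.3% | 22.6% | 12.1% | 18.9% |

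Simulation with 20,000 trials per setting agrees. BP: 7.0% and 8.8% at ICC 0.01, 9.1% and 13.0% at 0.02. CRC, with 192 per arm: 6.3% and 7.9%, then 7.8% and 10.6%.

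**Step 3: what each ICC means.** The between-counsellor SD in systolic change is √(ICC × 351.56): 1.9 mmHg at 0.01, 2.7 at 0.02 and 4.2 at 0.05. For CRC, √(ICC × 0.35 × 0.65) gives 4.8, 6.7 and 10.7 percentage points. At ICC 0.05 counsellors would differ by almost as much as the whole 5 mmHg target, so that row is an extreme and not a central estimate.

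**Step 4: BP power if the level is counted.** Power = Φ(5/√((180 + 351.56·DEFF)/200) − 1.96). At ICC 0.01 this is 81.3% (k = 8) or 76.0% (k = 4); at ICC 0.02 it is 76.2% or 66.6%. Small-sample degrees of freedom would lower these further.

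**The case against.** **No inflation is shown.** A reader might infer that the planned tests certainly exceed 5%. The document does not support that: it gives no ICC, caseload or staff count, and at ICC 0 the tests hold their level. If an intervention affects nobody, its counsellors cannot differ through it. This stands, and it is why the point is conditional.

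**The largest figures are implausible.** A reader might take the ICC 0.05 row as the likely size. It needs a counsellor SD of 4.2 mmHg from a few sessions or, for CRC, some navigators two SDs below 35%, at about 14% (35 − 2 × 10.7). This also stands, and the conclusion rests on the lower rows. For the same reason I do not assume that navigators, whose sessions concern CRC screening, produce clustering in BP.

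**Staff can be regarded as fixed.** With individual randomisation, the unadjusted test is interpretable for the interventions as delivered by these people. That is a legitimate target but a narrower one than the article's stated purpose of translation.

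**Fidelity work limits variation.** Training, booster sessions and retraining are meant to standardise delivery. They do not show that outcomes differ by counsellor, but nor do they justify assuming zero.

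**Continuity is not stated.** The article does not say that a man keeps the same interventionist. If staff share cases, simple nesting describes the data less well and clustering weakens.

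**The SAP is unseen.** It may add the level, and naming one primary between-persons factor does not exclude others. But the article does not leave clustering open: it chooses the CRC levels, and the choice misses the one level that the design nests in arm.

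**Conclusion.** The concern holds in conditional form. Interventionists are nested in arm and neither primary analysis, as written, includes them. If outcomes vary by interventionist, intervals will be too narrow and type I error will exceed 5% for conclusions that reach beyond these staff.

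Under the assumptions above, the excess over 5% is about 1 to 4 percentage points at ICC 0.01. At ICC 0.02 it is about 4 to 8 points for BP and 3 to 6 for CRC. It is larger only if counsellors differ greatly.

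The stated 86% BP power is not miscalculated, but it holds only with no interventionist effect. For CRC the planned effect leaves ample room: even with both arms clustered at ICC 0.01 and only 3 interventionists per arm, power at 200 per group is 97.7%. The practical exposure is therefore mainly in BP.

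**What to change.** 1. Record the interventionist who delivered each man's first session, and use that as the grouping variable. Because staff are not said to be randomised to men, this label may also carry some shop or calendar effect; say so when reporting.
2. Pre-specify, beside each primary result, a partially nested model with a random effect for MINT counsellor (BP) or navigator (CRC), the men in the other arm being treated as unclustered, and small-sample degrees of freedom. Make it the primary model only if there are enough interventionists to estimate the variance. State the number of interventionists and their caseloads.
3. In Sample size and power calculations, state that the 86% BP power assumes no interventionist effect.

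**Cost.** One identifier per man, which should be recoverable because all sessions are recorded and supervised, and some analysis work. No extra participants or procedures are needed. The change can still be made: Trial status reports 444 men recruited and follow-up to come. The downsides are wider intervals, lower power if counsellors differ, and an imprecise variance estimate when there are few of them, which is why the model sits beside the primary result by default.

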## Discussion

### Public health significance and implications for future research

This protocol will be a unique opportunity to test two interventions simultaneously, offering at least one intervention to each study participant regardless of randomized assignment, eliminating the need for a traditional control group and accompanying ethical issues. Our study will be one of the first to test patient navigation for CRC screening in a community-based setting, thus having the potential to reach individuals without access to regular primary care. These individuals, who are underserved by the healthcare system, are in greater need for preventive care than those with a regular source of primary care and are generally overlooked in clinic-based studies.

Future research should test other innovative methods of addressing health disparities among true community-based populations. Furthermore, our study addresses two health issues among urban black men, yet more research is needed to determine whether there are important differences produced by ethnicity or socioeconomic status within this diverse demographic which may deserve further attention. Finally, it is important to maintain effective programs past the length of a randomized control trial, thereby maintaining the trust of communities and continuing to address health disparities beyond the scope of individual research studies. Research into the efficacy of developing sustainable methods to address health disparities in black communities is essential.

## Trial status

The Mister B trial began recruitment in December of 2009. To date, we have recruited a total of 444 participants from 103 barbershops and other community organizations. Of those, 219 are randomized to receive the MINT intervention, 225 are randomized to receive the PN intervention. Participant recruitment will conclude in approximately four months, and participants will be followed for six months.

## Abbreviations

BMI: Body mass index; BP: Blood pressure; CEEP: Clarify-Empathize-Explain-Plan; CRC: Colorectal cancer; CT: Computed tomography; DBP: Diastolic blood pressure; FIT: Fecal Immunochemical Test; FOBT: Fecal Occult Blood Test; HTN: Hypertension; IPAQ-S: International Physical Activity Questionnaire – short version; IRB: Institutional review board; JNC-7: Seventh Report of the Joint National Committee on Prevention, Detection, Evaluation, and Treatment of High Blood Pressure; MET: Average metabolic equivalent; MINT: Motivational interviewing (lifestyle intervention); MISTER B: *M*ulti-Intervention Study to *I*mprove CRC *S*creening and *t*o *E*nhance *R*isk Reduction in *B*lack Men; MITI: Motivational Interviewing Treatment Integrity; NYC DOHMH: New York City Department of Health and Mental Hygiene; PN: Patient navigation; RA: Research assistant; SBP: Systolic blood pressure; SD: Standard deviation; TLC: Therapeutic lifestyle changes.
